#### Assessments

All assessments are self-reported and will be conducted online. Table 1 depicts an overview of the assessment instruments that will be used throughout each stage of the study. Primary outcome measures are disordered eating behaviors and attitudes (SEED, EDE-Q) [23,27]. Secondary outcome measures contain ED-related quality of life (ED-QOL) [28], self-stigma of seeking help [29], self-esteem, mastery and support [30], symptoms of depression and anxiety (PHQ-4) [31], repetitive negative thinking (PTQ) [32], motivation to change [33,34], and user satisfaction, as well as compliance and help-seeking attitudes and behaviors. Cost-effectiveness will be evaluated by means of the reported quality of life (EQ-5D) [35] and medical and societal costs (Trimbos/iMTA Questionnaire for Costs Associated with Psychiatric Illness: TiC-P) [36].

**Table 1 T1:** Overview of the assessment instruments used throughout each stage of the study

**Assessment**	**Screening**	**T0: Baseline**	**Weekly monitoring: even weeks**	**Weekly monitoring: uneven weeks**	**T1: Post-intervention**	**T2: 3-month follow-up**	**T3: 6-month follow-up**^2^
Weight Concern Scale (WCS)	X	-	-	-	-	-	-
Short Evaluation of Eating Disorders (SEED)	X	X	-	-	X	X	X
Short Evaluation of Eating Disorders II (SEED-II)	-	-	X	X	-	-	-
Demographics and other information	-	X	-	-	-	-	-
Monitoring questionnaire	-	-	X	X	-	-	-
Patient Health Questionnaire 4 (PHQ-4)	-	X	-	X	X	X	X
Perseverative Thinking Questionnaire (PTQ)	-	X	-	X	X	X	X
Eating Disorder Examination Questionnaire (EDE-Q)	-	X	-	-	X	X	X
Self-stigma of seeking help	-	X	-	-	X	X	X
Self-esteem, mastery and support	-	X	-	-	X	X	X
Eating Disorder-related Quality of Life (ED-QOL)		X	-	-	X	X	X
Motivation to change	-	X	-	-	X	X	X
Session Rating Scale (SRS)	-	-	X^1^	-	-	-	-
User satisfaction questionnaire	-	-	-	-	X^2^	-	-
Attrition follow-up question	-	-	X^3^	X^3^	X^3^	X^3^	X^3^
Help-seeking attitudes and behavior questionnaire	-	-	-	-	X	X	X
Quality of life (EuroQol: EQ-5D)	-	X	-	-	X	X	X
Trimbos/iMTA questionnaire for costs associated with psychiatric illness	-	X	-	-	X	X	X

^1^Only asked after participants’ first week of participation.

^2^Not sent to participants who are randomized to the waiting list control condition.

^3^Sent to participants who fail to complete the monitoring assessment, or the T1, T2 or T3 assessment, respectively.

The following variables will be tested as potential predictors or moderators of intervention response: demographic variables (age, gender, educational level), motivation to change (importance, ability and readiness to change), severity of ED symptoms (SEED, EDE-Q) [23,37], severity of symptoms of depression and anxiety (PHQ-4) [31], early working alliance (SRS) [38], and compliance.

Mediator variables and their corresponding dependent variable will be measured frequently throughout this study, at T0 and T1, as well as once every two weeks in between T0 and T1. The variables repetitive negative thinking (PTQ) [32] and symptoms of depression and anxiety (PHQ-4) [31] will be tested as mediators of intervention outcome, being symptoms of ED as measured by the SEED [23].

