The primary aim of the current study will be to investigate the effectiveness of (the different components of) Featback. The second aim is to investigate potential predicting, moderating, and mediating variables in order to gain insight into when or for whom this intervention works, as well as how it works. The third aim of this study is to report on the practical experiences of Featback, such as the user satisfaction and the (intensity of) use of the different components. Finally, the fourth aim of this study is to examine the cost-effectiveness of Featback.

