### Eating Disorder Examination Questionnaire (EDE-Q)

The EDE-Q [27] has been developed as a self-report questionnaire version of the Eating Disorder Examination (EDE) [41], a semi-structured interview measuring ED psychopathology. The EDE-Q assesses both the frequency of core ED behaviors and the core attitudinal features of ED pathology over the past 28 days. Items assessing the latter are answered on a 7-point Likert scale ranging from 0 ‘not one day/not at all’ to 6 ‘every day/markedly’, and include questions about restraint, concerns about weight, concerns about shape and concerns about eating. A global score of eating psychopathology will be calculated by summing and averaging all the individual items. Higher scores are indicative of a higher ED psychopathology. The EDE-Q has demonstrated reliability and validity (see Berg et al., [42], for a review).

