### Short Evaluation of Eating Disorders (SEED)

The SEED [23] is a brief self-report measure for the assessment of key ED symptoms. It assesses the three main symptoms of anorexia nervosa (degree of underweight, fear of weight gain, and distortion of body perception) and bulimia nervosa (amount of binge eating, amount of compensatory behavior, and over concern with body shape and weight). Total severity indexes can be calculated for each of the two diagnoses (range 0–3), with higher scores reflecting higher severity indexes. The behavioral measures (bingeing, excessive exercising, and compensatory behaviors) are assessed over the previous four weeks. The SEED has demonstrated construct validity and criterion-related validity, and was furthermore shown to be sensitive to symptom change [23].

Given that the SEED will be administered every week during the intervention period as well, the four-week timeframe for the behavioral measures is adapted to a timeframe of one week. This adapted questionnaire will be referred to as SEED-II.

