### Sample size

The sample size calculation is based on an expected small between-group effect size (Cohen’s *d* = 0.32) [45]. The calculation is conducted by the software program Power Analysis and Sample Size (PASS, 2008). The primary analysis will concern the hypothesis that the average post-intervention level of eating pathology in the waiting list control condition is higher than the average level of eating pathology in the three active intervention conditions. Assuming an alpha of 0.05 and a power of 0.80 (β-1) in a one-way ANOVA study, we need sample sizes of 79 participants in each of the four groups whose means are to be compared using a planned comparison. Taking into account a baseline variable (e.g., T0 assessment) for which we assume a Pearson correlation of 0.5 with the outcome variable, and thus explaining 25% of the variance of the outcome variable, the sample size per group can be reduced by 25% and is thus calculated as 0.75 × 79 = 60 per group. In order to account for dropout, recently reviewed to be approximately 30% for Internet-based interventions [46], the definitive number of participants we will need to recruit is 10/7 × 60 = 86 participants per group, resulting in 344 in total.

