### Statistical analyses

All statistical analyses will be performed in SPSS version 19. A two-tailed significance level of *α* = 0.05 will be used throughout the analyses. Both intent-to-treat and completers analyses will be conducted. Intent-to-treat analyses will include every participant who is randomly allocated to the intervention, regardless of withdrawal or deviation from the protocol [47]. Someone will be considered a completer in case he/she has completed both T0 and T1 assessments, and at least five monitoring assessments.

Pre-treatment differences between the conditions will be investigated using *χ*^*2*^ tests for categorical variables and ANOVAs for continuous variables. Linear mixed model analyses will be used to investigate the effectiveness and maintenance effects of Featback. Time contrasts will be created by means of dummy-coding. Within- and between-group effect sizes (Cohen’s *d*) [48] will be calculated based on the pooled standard deviation. As recommended by Frazier, Tix and Barron [49], potential categorical predictor or moderator variables will be dummy coded, and potential continuous predictor or moderator variables will be standardized. A significant two-way interaction between predictor and time indicates a predictor effect. A significant three-way interaction between time, condition and moderator, indicates a moderator effect. Significant moderator effects of continuous variables will be interpreted by dichotomizing the moderator variable into subgroups of participants who score either low or high (e.g., below or above the sample mean) on the moderator variable. Separate mixed model analyses will then be repeated to examine interactions between condition and time within the low and high subgroups.

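### Two primary instruments give up to three total scores, the sized hypothesis names none of them, and an unadjusted 0.05 applies throughout

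*Protocol article*

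**What the plan says.** All references are to the protocol article.

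- **Assessments**: "Primary outcome measures are disordered eating behaviors and attitudes (SEED, EDE-Q". No single score is picked.
- **Short Evaluation of Eating Disorders (SEED)**: "Total severity indexes can be calculated for each of the two diagnoses", namely anorexia nervosa and bulimia nervosa. No combined SEED score is described.
- **Eating Disorder Examination Questionnaire (EDE-Q)**: "A global score of eating psychopathology will be calculated by summing and averaging all the individual items".
- **Sample size**: the primary hypothesis is that "the average post-intervention level of eating pathology in the waiting list control condition is higher than" the average level in the three active conditions. The score that measures this level is not named. The calculation reads "Assuming an alpha of 0.05 and a power of 0.80 (β-1) in a one-way ANOVA study", with d = 0.32, a baseline correlation of 0.5 and 30% dropout.
- **Statistical analyses**: "A two-tailed significance level of *α* = 0.05 will be used throughout the analyses". No adjustment is mentioned.
- **Mediator text under Assessments, and the cross-lagged paragraph under Statistical analyses**: the outcome for mediation is the SEED, and the cross-lagged paragraph then speaks of the primary outcome in the singular.
- **Background, aims**: "The primary aim of the current study will be to investigate the effectiveness of (the different components of) Featback".

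**The concern.** The primary outcome is plural in the Assessments section and singular in the sample size hypothesis and the cross-lagged paragraph, and nothing links the two. The candidate scores are not interchangeable: the two SEED indexes describe different disorders, and the EDE-Q global score summarises attitudes across both. With two-tailed 0.05 fixed for every analysis, the article allows the central hypothesis to be tested on each score at the full level. A positive finding on whichever score reached significance could then be reported as the primary result, with an error rate above the nominal 5%.

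A related but smaller matter is that the primary aim includes the components of the intervention, while the only contrast that was sized pools all three active arms. A positive pooled result cannot show whether support adds anything, and a null result between support levels may simply reflect low precision.

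**Working it through.** **1. The plan's own figure.** Inputs (Sample size): d = 0.32, alpha 0.05, power 0.80, four equal groups, one planned comparison of one group with the mean of three.

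- The variance of the contrast is SD² × (1 + 1/3)/n.
- One-sided 0.05 gives 81 per group. A 1-df contrast with f = d/2 = 0.16 gives 78. The stated 79 lies between them, so it is reproduced within tolerance.
- Two-sided 0.05 at d = 0.32 would give 103 per group.
- Later steps: 0.75 × 79 = 59.25, rounded up to 60; 60 × 10/7 = 85.7, rounded up to 86; 4 × 86 = 344. These agree with the article.

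The calculation covers one test on one score.

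**2. Number of candidate primary scores.** EDE-Q global (1) + SEED indexes (2) = 3 totals. If only one SEED index is used, there are 2. EDE-Q behaviour frequencies are not counted.

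**3. Chance of at least one false positive on the pooled contrast, each score at two-sided 0.05.**

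- Independent scores: 1 − 0.95³ = 14.3%; 1 − 0.95² = 9.75%.
- Correlated scores: simulation of equicorrelated normal test statistics, 2 million draws. The correlation is an assumption.

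| Correlation | Three scores | Two scores |
|---|---|---|
| 0 | 14.3% | 9.75% |
| 0.3 | 13.6% | 9.5% |
| 0.5 | 12.5% | 9.1% |
| 0.7 | 10.9% | 8.3% |
| 0.8 | 9.8% | 7.8% |
| 0.9 | 8.4% | 7.0% |

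**4. Secondary check: comparisons between support levels.** Inputs: 60 evaluable per arm and r = 0.5, so the variance of an arm mean is 0.75/60 = 0.0125 in units of SD². For 80% power at two-sided 0.05 the multiplier is 1.960 + 0.842 = 2.802.

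- Support (two arms) against none (one arm): SE = √(0.0125 × 1.5) = 0.137; detectable d = 2.802 × 0.137 = 0.38.
- Frequent against infrequent: SE = √(0.0125 × 2) = 0.158; detectable d = 2.802 × 0.158 = 0.44.

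Both exceed the planned 0.32. If a difference of 0.32 were assumed between arms, power would be about 65% and 52% respectively.

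**The case against.** **The error rate is conditional.** A reader might infer that the trial's false-positive rate simply is 11-14%. The article does not support that. It would require that all three scores are tested as primary, that any one significant score counts as success, and that the scores correlate at no more than about 0.7. The article names two instruments, says only that SEED indexes can be calculated, states no success rule and gives no correlation. The scores measure overlapping pathology, so a higher correlation is possible. This objection stands, and the size is therefore given as a conditional range. It does not remove the point, because every case in the table exceeds 5%.

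**A later plan may settle it.** The article does state a single primary hypothesis, and an analysis plan could name its score. That is fair. However, the level of 0.05 throughout is a stated rule and not a silence, so any multiplicity adjustment would have to depart from it.

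**Comparisons between active arms.** A reader might also infer that the component question has no analysis at all. That goes too far. Linear mixed models are planned for effectiveness, and the Discussion says the longer-term data for the three forms of the intervention will be examined. The order and coding of such contrasts are commonly left to an analysis plan. What remains is that these comparisons are not sized. Nor does the article plan to conclude equivalence; its Background notes that two earlier null results on support frequency came from small samples.

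**The choice of score.** It is tempting to say that the EDE-Q should simply be made the sole primary outcome. That would clash with the mediation text, where the SEED is the outcome and is then treated as the primary one.

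**Conclusion.** The concern holds in limited form. The article leaves open which of up to three total scores carries its primary hypothesis and fixes an unadjusted two-tailed 0.05. If any one significant score is accepted as success, the false-positive risk on the pooled contrast is about 8-14% for three scores and 7-10% for two, over assumed correlations from 0.9 to 0. These figures cover that single contrast only.

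The limited precision between support levels is a secondary note. With the plan's own 60 evaluable per arm and r = 0.5, detectable effects are about d = 0.38 and d = 0.44. This bears on how those results are reported; it does not show that the comparisons are missing.

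**What to change.** Before outcomes are analysed by condition, choose one of two routes for the Sample size contrast (waiting list against the mean of the three active arms) at T1:

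1. **Holm across the primary scores.** With three scores, compare the ordered p-values with 0.05/3, 0.05/2 and 0.05, stopping at the first that fails. List exactly which scores are in the family.
2. **One named score.** State which score carries the hypothesis and make the others secondary. Reconcile the choice with the mediator text and the cross-lagged paragraph, either by aligning the score or by rewording the singular reference to the primary outcome there.

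In addition, report the comparisons between support levels with confidence intervals, give the detectable effects above, and state that a non-significant difference will not be read as equivalence.

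**Cost.** Only analysis wording changes, so completed enrolment is no obstacle. Holm costs power: for a given score at d = 0.32 with 60 per arm, the pooled contrast has about 70% power at two-sided 0.05 and about 53% at the strictest step, 0.05/3. That 53% is a lower bound for a single score under Holm. Naming one score avoids this loss, but the other scores, and possibly a whole instrument, lose primary status.

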### Weight Concern Scale (WCS)

The WCS [39] assesses fear of weight gain, worry about weight and body shape, importance of weight, diet history, and perceived fatness. The WCS has demonstrated test-retest reliability and predictive validity [39] and was furthermore found valid in identifying students at risk for the development of an ED [40].

### Demographics and other information

A self-designed questionnaire will assess gender, age, educational level, country of origin and work situation, perceived severity levels of eating problems (including a question asking participants whether they have ever been diagnosed with an ED), and treatment status. Furthermore, the questionnaire asks participants how many days they have been sick during the previous three months, their average Internet usage during a typical week/day, and their average school/work performance during the previous three months.

### Eating Disorder Examination Questionnaire (EDE-Q)

The EDE-Q [27] has been developed as a self-report questionnaire version of the Eating Disorder Examination (EDE) [41], a semi-structured interview measuring ED psychopathology. The EDE-Q assesses both the frequency of core ED behaviors and the core attitudinal features of ED pathology over the past 28 days. Items assessing the latter are answered on a 7-point Likert scale ranging from 0 ‘not one day/not at all’ to 6 ‘every day/markedly’, and include questions about restraint, concerns about weight, concerns about shape and concerns about eating. A global score of eating psychopathology will be calculated by summing and averaging all the individual items. Higher scores are indicative of a higher ED psychopathology. The EDE-Q has demonstrated reliability and validity (see Berg et al., [42], for a review).

### Short Evaluation of Eating Disorders (SEED)

The SEED [23] is a brief self-report measure for the assessment of key ED symptoms. It assesses the three main symptoms of anorexia nervosa (degree of underweight, fear of weight gain, and distortion of body perception) and bulimia nervosa (amount of binge eating, amount of compensatory behavior, and over concern with body shape and weight). Total severity indexes can be calculated for each of the two diagnoses (range 0–3), with higher scores reflecting higher severity indexes. The behavioral measures (bingeing, excessive exercising, and compensatory behaviors) are assessed over the previous four weeks. The SEED has demonstrated construct validity and criterion-related validity, and was furthermore shown to be sensitive to symptom change [23].

Given that the SEED will be administered every week during the intervention period as well, the four-week timeframe for the behavioral measures is adapted to a timeframe of one week. This adapted questionnaire will be referred to as SEED-II.

### The Patient Health Questionnaire (PHQ-4)

The PHQ–4 [31] will be used to assess symptoms of depression and anxiety. The PHQ-4 consists of four items: two core anxiety items and two core depression items. Items can be answered on a 4-point Likert scale ranging from 0 ‘not at all’ to 3 ‘nearly every day’. A total score (range 0–12) can be calculated by summing the scores of all four items. Higher scores are indicative of a higher pathology. Factorial and construct validity were demonstrated for the PHQ-4 [31].

### Perseverative Thinking Questionnaire (PTQ)

The PTQ [32] will be used as a global measure of repetitive negative thinking (e.g., worry and rumination). The questionnaire consists of 15 items assessing the repetitiveness, intrusiveness, difficulties to disengage, and unproductiveness of repetitive negative thinking, as well as the degree to which it captures mental capacity. The scale of the items ranges from 0 ‘never’ to 4 ‘almost always’ and assesses how often each of the characteristics as described above applies to the participants’ thinking process. The Dutch PTQ demonstrated good internal consistency and satisfactory stability [32]. For the current study, we adapted the timeframe from ‘in general’ to ‘in the previous four weeks’ (T0, T1, T2, and T3 assessment) or ‘in the previous week’ (during the intervention period) respectively, in order to increase the ability to detect weekly or monthly change.

### Self-stigma of seeking help

The 10-item self-stigma of seeking help [29] questionnaire will be used to assess one’s self-stigma towards seeking psychological help. The questionnaire was developed to measure concerns about the loss of self-esteem and an overall sense of loss of value a person would feel if he/she would decide to seek help from a psychologist or any other mental health professional. Answers can be rated on a 5-point Likert scale ranging from ‘strongly disagree’ to ‘strongly agree’. Higher scores reflect higher self-stigma or a more negative stigma toward seeking psychological help. The questionnaire was found to have good psychometric properties [29].

### Self-esteem, mastery and support

Starting from existing instruments, Bovier et al. [30] used factor analyses to develop four brief scales for the measurement of self-esteem (four items), mastery (four items), affective social support (two items), and confident/problem solving social support (four items). Affective support refers to the availability of people who express emotional involvement with, and care for a person, whereas confident/problem solving support refers to the availability of an individual one can confide in and receive advice from when a challenging situation occurs [30]. Items of all four brief scales can be answered on a 5-point Likert scale. Higher scores represent higher self-esteem, mastery, affective- and confident support, respectively. All four scales were found to demonstrate good internal and construct validity [30].

### Eating Disorders Quality of Life (ED-QOL)

The ED-QOL [28] is a disease-specific health-related quality of life measurement designed for individuals with ED symptoms. The ED-QOL consists of 25 items, assessing the influence of eating behaviors/body weight in four subscales: psychological (nine items), physical/cognitive (six items), financial (five items), and work/school (five items). A total score can be calculated by averaging the items of the four subscales. Higher scores are indicative of a lower quality of life. The ED-QOL demonstrated good convergent and discriminative validity, as well as test-retest reliability [28].

### Motivation to change

Three items will be used to assess participants’ motivation to change [33,34]: their perceived importance to change*,* their perceived ability/confidence to change, and their readiness to change. Questions can be answered on a 10-point Likert scale.

### Session rating scale (SRS)

The SRS [38] will be used to measure the working alliance between participants and their coaches, as well as to measure the perceived degree of support from the automated feedback messages and coaches, respectively. The SRS consists of four items that assess four aspects of the working alliance: the relational bond, the degree to which desired goals and topics of the individual are discussed, an evaluation of the therapist’s approach or method used, and an evaluation of the overall perception of the session by the individual. Instead of using a visual analogue scale, an 11-point Likert scale will be used to answer each of the four items, with ‘0’ depicting a negative response and ‘10’ depicting a positive response. The SRS demonstrated a high test-retest and internal consistency reliability, as well as an acceptable validity [38].

